### Data management and statistical analysis

The data will be analyzed using SPSS software version 25, and p-value > 0.05 will consider a statistically significant level. First, the Kolmogorov‐Smirnov test will use to examine the normal distribution of data. After determining the normal distribution of data, to compare statistical differences of demographic data in two groups, an independent t-test, Chi-square test, and Fisher's exact test will be used. Also, for analyzing outcome variables, **r**epeated-measures analysis of variance (ANOVA) with a pairwise comparison of groups with Bonferroni correction, independent t-test, and Chi-square will determine the differences between the groups. **Sample size**

The sample size was calculated based on the results of Gözde Birsbir et al. (2016) study (18). A sample size of 70 pregnant women (35 in each group) was estimated. A two-sided t-test of difference between means with the power of 90%, the type one error equal to 0.05, mean difference of 21 between groups, and standard deviation of 7.2 was consider calculating the sample size. We accounted 20% attrition rate in estimating the sample size.

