**Procedures**

A convenient sampling approach will be used, and a consecutive sample of pregnant women attending the selected prenatal clinic (located in Baharlou hospital) for receiving their routine prenatal care will be evaluated by their medical records for inclusion and exclusion criteria, by a colleague not involving in the study. Afterward, the objectives and goal of the study will be explained to eligible pregnant women, and after filing the consent form, they will be asked to complete the W-DEQ version A. women with a score of 38 and above (moderate and high FOC score) will be enrolled the study.

A randomized allocation into two groups of intervention and control with a 1: 1 ratio will be taken place during the routine prenatal visit in the hospital by a colleague who will be not involved in the study and computerized generated random sequences. In both intervention and control groups, the Tele-midwifery application will be installed on their smartphones during their prenatal visit. This application will only allow access to the questionnaires in the post-test, and follow-up stages for the participants in the control group. To prevent information contamination to the control group, after installing the application and before activating their account, women must select their group type as A or B. In addition, we will ask women in both groups to avoid sharing the contents of the application with each other for the duration of the trial. The Tele-midwifery application have two main stages for answering the questions. After filling the baseline questionnaire in the initial registration, including demographic, W-DEQ, and CBSE questionnaires, each group’s participants will complete the W-DEQ and CBSE questionnaires again at 34-36 weeks (after eight weeks of receiving the intervention). Participants will be also asked to inform the researcher by sending a message after hospitalization for their birth, whether in the Tele-midwifery application or by contacting the researcher directly by her phone number. Afterward, the W-DEQ version B questionnaire will appear in the application within the first two hours after birth, and the birth mode will be recorded. The investigators, care providers, data collectors, and statisticians will be masked from the allocation.

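### The protocol's only stated significance threshold has its inequality reversed, contradicting the type I error of 0.05 used for the sample size

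*Protocol*

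**What the plan says.** The Data management and statistical analysis section of the protocol opens with the software and then the criterion for significance: "p-value > 0.05 will consider a statistically significant level". The sentence is not limited to any one outcome or test. The same section then names a normality check, tests for the demographic data, and, for the outcomes, repeated-measures ANOVA with Bonferroni-corrected pairwise comparisons, t-tests and chi-square tests.

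Six sentences after the criterion, in the sample-size paragraph of that section, the plan gives its error rates: "A two-sided t-test of difference between means with the power of 90" percent, and "the type one error equal to 0.05".

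No other part of the protocol gives a threshold. The Project summary lists the tests without one, and the Bonferroni statement carries no figure of its own.

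**The concern.** A significance test rejects the null hypothesis when the p-value is small. The printed sentence attaches significance to large p-values. It therefore disagrees with the type I error on which the same section sizes the trial, and nothing elsewhere in the protocol states the right direction.

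The sentence matters because it is general. It covers the tests behind all three hypotheses in Study goals and objectives: fear of childbirth, self-efficacy and number of caesarean sections. A protocol is the record against which the reported analysis is later checked, and on this line it says the opposite of what its sample-size paragraph assumes.

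**Working it through.** **Inputs, all from the protocol**

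- Criterion as printed: p > 0.05 counts as significant (Data management and statistical analysis).
- Type I error 0.05, two-sided t-test, power 90% (sample-size paragraph).
- Assumed effect: "mean difference of 21 between groups, and standard deviation of 7.2".
- Size: "A sample size of 70 pregnant women (35 in each group) was estimated", with 20% attrition allowed for, so 35 × (1 − 0.20) = 28 completers per group.

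**Step 1. The type I error implied by each direction of the sign.** When there is no true effect, a valid p-value from a continuous test is uniform on 0 to 1.

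- As printed: P(p > 0.05) = 1 − 0.05 = 0.95.
- Sign reversed: P(p < 0.05) = 0.05.

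Only the second agrees with the protocol's own figure of 0.05.

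**Step 2. Check by simulation.** In 100,000 two-sample t-tests with 28 per group and no true difference, p exceeded 0.05 in a proportion 0.94937 and fell below it in 0.05063. The Monte Carlo standard error is √(0.95 × 0.05 / 100,000) = 0.0007, so both agree with step 1.

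**Step 3. Behaviour under a true effect.**

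- For an effect at which the test has exactly 90% power, the printed rule would call it significant with probability 1 − 0.90 = 0.10 and so miss it 90% of the time.
- At the protocol's own assumptions the effect is far larger than that. With difference 21, SD 7.2 and 28 per group, the expected test statistic is about 21 / (7.2 × √(2/28)) = 21 / 1.924 = 10.9, so p is practically always far below 0.05. In 20,000 simulated trials the printed rule called the effect significant in none, and the rule with the sign reversed in all.

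**Step 4. The two statements side by side.**

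| Statement in the protocol | Implied type I error |
|---|---|
| Criterion as printed (p > 0.05) | 0.95 |
| Sample-size paragraph | 0.05 |
| Criterion with sign reversed (p < 0.05) | 0.05 |

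Reversing the sign removes the contradiction completely. Whether 70 women follows from the stated difference and SD is a separate question and is not used here.

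**The case against.** The strongest reply is that this is a slip of the keyboard whose meaning can be recovered from the same section. A type I error of 0.05 with 90% power is compatible only with p < 0.05, so only one sensible reading is left. The protocol has other language slips of this kind. The Project summary uses the wrong verb for forming a hypothesis. A sentence in the rationale reads as if the intervention might raise the number of caesarean sections, whereas the third objective expects fewer. On this view the realistic risk to the trial's conclusions is close to nil.

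Most of this stands. A reader might infer from the printed rule that the trial will declare effects where there are none and overlook real ones, with every conclusion turned round. The documents do not support that. The stated alpha and power show the intent, and nothing suggests that anyone chose the reversed rule. The figures 0.95 and 90% describe the literal sentence and are simply the complements of alpha and power; they do not forecast this trial's results. Nor is the sentence the whole decision procedure, since pairwise comparisons also carry a Bonferroni correction.

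What the reply does not remove is the error itself. The wrong sign stands on the one line that fixes the threshold, and the reader has to correct it by inference from another paragraph.

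**Conclusion.** The point holds as an error of wording and an internal contradiction. The protocol's only stated significance threshold has its inequality reversed and conflicts with the two-sided type I error of 0.05 in the same section. Read literally, its type I error is 0.95 instead of 0.05. It is almost certainly a typing error, and its likely effect on the actual analysis is small. It still warrants correction, because the sentence sets the criterion for every outcome and the error is certain.

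The conclusion rests on two assumptions: that p-values are valid, hence uniform under no effect, and that the sign appears in the source document as it does in the text reviewed. The sign stands in running prose with no trace of redaction, but the source pages could not be inspected.

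**What to change.** Replace the criterion with: *a two-sided p-value < 0.05 will be considered statistically significant.* This matches the two-sided test and type I error already in the sample-size paragraph. Leave the Bonferroni correction for pairwise comparisons as stated.

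The cost is one line of protocol text. The error gives no reason to alter the tests, the sample size, the data collection or the way results are reported, and the correction has no downside.

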**Research protocol**

**Project summary**

Fear of childbirth (FOC) is a risk factor for maternal and child adverse outcomes and needs to be addressed during pregnancy. In this study, we aim to determine the effect of an mHealth application based on continuous support and education on FOC, self-efficacy, and birth mode in primiparous women. This study will be a single-center, Randomized Controlled Trial (RCT). It will conduct on seventy primiparous pregnant women with FOC attending a university-dependent governmental hospital in Tehran, Iran. Women who meet the inclusion criteria will randomly assign to two parallel intervention and control groups. Study participants in the intervention group will receive an mHealth application named Tele-midwifery, an interactive application based on multipurpose approaches, such as education and consultation, emphasizing continuous care for eight weeks. Women in the control group will receive routine prenatal care. FOC and self-efficacy will be measured via Wijma Delivery Expectancy/Experience (W-DEQ) questionnaire and Childbirth Self-efficacy Inventory (CBSEI), respectively. Data will be collected at the beginning of the study, 36 weeks of pregnancy, and after childbirth. Data will be analyzed by SPSS-25 using Chi-square, Fisher’s exact test, independent t-tests, and repeated-measures analysis of variance. We hypnotize that the intervention in this study will improve the FOC score, increase self-efficacy, and lower the number of C-sections.

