### Methodology

**Outcomes**

The primary outcome of this study will be change in FOC score, and the secondary outcomes will be change in childbirth self-efficacy score, and birth mode.

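### The protocol fixes repeated-measures ANOVA and t-tests without a baseline covariate; adjusting for the baseline score already collected is at least as powerful at realistic correlations and costs almost nothing

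*Protocol*

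**What the plan says.** The Data management and statistical analysis section names repeated-measures "analysis of variance (ANOVA) with a pairwise comparison of groups with Bonferroni correction, independent t-test" and chi-square as the means of comparing the groups on the outcomes. The Project summary lists the same family of methods. Neither place mentions a baseline covariate.

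Under Outcomes: "The primary outcome of this study will be change in FOC score". No time point is attached to it.

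On timing, the Project summary states: "Data will be collected at the beginning of the study, 36 weeks of pregnancy, and after childbirth". Under Procedures, before enrolment "they will be asked to complete the W-DEQ version A", and the baseline set at registration includes both W-DEQ and CBSEI. Then "each group’s participants will complete the W-DEQ and CBSE questionnaires again at 34-36 weeks (after eight weeks of receiving the intervention". After delivery the instrument changes: "the W-DEQ version B questionnaire will appear in the application within the first two hours after birth". W-DEQ therefore has three measurements, the last on version B. CBSEI is scheduled at only two.

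On loss to follow-up: "We accounted 20% attrition rate in estimating the sample size".

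The text does not say whether baseline is a level of the time factor, whether the group main effect or the group-by-time term is the treatment test, or whether the t-tests use follow-up or change scores.

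**The concern.** The baseline score is usually a good predictor of the follow-up score, and here it is collected before any outcome. An analysis that leaves it out, or uses it only by subtraction or as another time level, generally has less power than one that adjusts for it. With about 28 evaluable women per arm, that can matter.

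Two further consequences depend on how the ANOVA is read.

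- **Dilution.** Randomisation makes the expected group difference at baseline zero. If baseline is a time level and the group main effect is the test, that zero is averaged into the estimated effect.
- **Case deletion.** Conventional repeated-measures ANOVA uses only women with every time point. A woman with a valid 34-36-week W-DEQ but no post-birth form drops out of that analysis altogether.

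**Working it through.** **The plan's own figure.** The inputs in the Sample size paragraph are a difference of 21, SD 7.2, two-sided 0.05, 90% power and 20% attrition. The standardised effect is 21/7.2 = 2.92. The exact t-test has 76.1% power with 3 per arm and 92.7% with 4. So 4 per arm are needed, which is 4/0.8 = 5 per arm or 10 in total after attrition. The stated 70 (35 per arm) is not reproduced. Working back, 35 × 0.8 = 28 completers per arm give 90% power at a standardised effect of about 0.88, which means an SD of about 24 if the difference is 21. The mismatch is a separate matter. It is relevant here because 2.92 cannot be taken as a secure effect size.

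**Inputs for the comparison.** n = 28 per arm (35 × 0.8, from the protocol). Assumed, because the protocol gives no figure: an effect d = 0.7 SD at both follow-ups, and a common correlation r between all visits. The test is two-sided at 0.05.

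**Formulas.** A t-type test has noncentrality √(n/2) × effect/SD, and √14 × 0.7 = 2.62 for the follow-up score alone.

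- Follow-up t-test: variance 1, 54 df, noncentrality 2.62.
- Change-score t-test: variance 2(1 − r). Noncentrality 2.21, 2.62, 3.38 at r = 0.3, 0.5, 0.7.
- ANCOVA at one visit: variance 1 − r² (0.91, 0.75, 0.51), 53 df. Noncentrality 2.75, 3.02, 3.67.
- Group main effect, three levels: effect (0 + d + d)/3 = 2d/3, variance (1 + 2r)/3. Noncentrality 2.39, 2.14, 1.95.
- Group main effect, two levels (CBSEI): effect (0 + d)/2 = d/2, variance (1 + r)/2. Noncentrality 1.62, 1.51, 1.42.
- Group-by-time, three levels: F on 2 and 108 df, noncentrality 14 × (2/3)d²/(1 − r) = 4.57/(1 − r), which is 6.53, 9.15, 15.24.

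| Power, d = 0.7, 28 per arm | r = 0 | r = 0.3 | r = 0.5 | r = 0.7 |
|---|---|---|---|---|
| ANCOVA, one visit | 73% | 77% | 84% | 95% |
| Follow-up t-test | 73% | 73% | 73% | 73% |
| Change-score t-test | 44% | 58% | 73% | 91% |
| Group-by-time, 3 levels | 46% | 61% | 77% | 94% |
| Group main effect, 3 levels | 84% | 65% | 56% | 48% |
| Group main effect, 2 levels (CBSEI) | 44% | 36% | 32% | 29% |

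Allowing for chance baseline imbalance lowers the ANCOVA row by up to 0.8 points. At r = 0 it then falls just below the follow-up t-test (72.2% against 73.0%).

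For CBSEI, with two visits, the group-by-time test is identical to the change-score t-test.

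**At other effect sizes.** At d = 0.88 and r = 0.5: ANCOVA 96%, group-by-time 93%, follow-up and change t-tests 90%, three-level main effect 75%. At the stated 2.92, every row is about 100% at every r shown.

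**Case deletion.** If, for illustration, 10% were lost at each follow-up, a 34-36-week analysis would keep 35 × 0.9 = 31.5 per arm. One that requires all three visits would keep 35 × 0.9 × 0.9 = 28.4.

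**The case against.** The strongest reply is that both named methods are valid under randomisation, so this is a matter of efficiency, and that most of the apparent damage depends on a reading the protocol does not state. Much of that stands.

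- A reader might infer that the trial will report a diluted effect. The documents do not support that. The primary outcome is a change, which points to group-by-time or a change contrast, and neither is diluted by a zero baseline difference. Baseline as a time level is a natural inference from three measurements, but it is not written, and the group main effect is not named as the test.
- A reader might infer that the t-tests ignore baseline. They would if run on follow-up scores, but the protocol does not say which scores they use.
- A reader might infer that women without a post-birth form vanish from every antenatal comparison, and that loss will differ between arms. Deletion is a property of conventional repeated-measures ANOVA. It does not touch separate t-tests at each visit, and missing-data rules may sit in an SAP that is not shown. Differential loss is speculation: both arms have the app and report the birth by the same route, and controls are asked to keep it installed.
- At the planned effect there is no power to gain. At r = 0 the three-level main effect has more power than ANCOVA (84% against 73%). Entry restricted to W-DEQ 38 and above may lower r, and the change to version B after birth makes equal correlations and equal effects less certain.

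What remains is that the protocol positively names its outcome methods, none adjusts for baseline, and the adjustment needs only data it already collects.

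**Conclusion.** The point holds as an efficiency improvement to a method the protocol fixes, not as an error that invalidates the analysis.

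- Against a follow-up t-test, ANCOVA gains 4, 11 and 22 percentage points at r = 0.3, 0.5 and 0.7.
- Against a change-score t-test, the gain is 18 to 19, 11 and 4 points.
- Against group-by-time, it is 16, 8 and about 1 point, so negligible at high correlation.
- Only if the group main effect with baseline as a level were the test would the estimate shrink, to two thirds for W-DEQ and one half for CBSEI.

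These figures rest on 28 per arm, an assumed 0.7 SD effect equal at both follow-ups, and assumed equal correlations. At 21/7.2 the choice makes no difference to power. It matters if the true standardised effect is smaller, and the sample size's failure to follow from its inputs is a reason not to rule that out. At r = 0 ANCOVA gains nothing and costs one degree of freedom, under 1 point of power. The loss of valid 34-36-week scores applies to the repeated-measures ANOVA itself, whatever the effect size.

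**What to change.** - Analyse the 34-36-week W-DEQ A by ANCOVA on group and baseline W-DEQ A, including every randomised woman with that score.
- Do the same for CBSEI with its own baseline.
- If the follow-ups are modelled jointly, use a linear mixed model with baseline as a covariate, not as a time level. This also uses women with only one follow-up.
- State that the ANOVA group main effect with baseline as a level is not the treatment test.

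The cost is a change of wording and one degree of freedom, with no new data, visits or participants; SPSS 25 runs both models. Two limits should be stated. ANCOVA at 34-36 weeks still omits women who lack that score. Making that analysis primary also settles the primary time point, which the protocol leaves open, so the sponsor should record it as a deliberate choice.

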**Measures**

The FOC will be measured using W-DEQ versions A and B. W-DEQ version A evaluates women's prenatal expectances before childbirth, and W-DEQ version B evaluates experiences with recent childbirth. Each version contains 33 items with a 6-point Likert scale ranging from 0 (extremely) to 5 (not at all), and scores range from 0 to 165, with higher scores indicating higher fear of childbirth (12). According to this questionnaire, a score less than or equal to 37 represent mild fear, a score of 38-65 represents a moderate level, 66-84 represents high level of fear, and a score more than 85 shows a severe level of fear. The reliability of the W-DEQ version A and B questionnaire for nulliparous women was confirmed with Cronbach's alpha of 0.89 and 0.92, respectively (12). The validity and reliability of the Persian version of this questionnaire for Iranian women have been confirmed (13).

The Childbirth Self-Efficacy Inventory (CBSEI) is a self-report instrument that measures outcome expectancies (OE) and efficacy expectancies (EE) for coping with an approaching childbirth experience. This questionnaire has two parts and 62 items that scored on a ten-point Likert scale (1= not at all; 10= completely sure), with a higher score indicating greater childbirth self-efficacy. The reliability of the questionnaire has been confirmed with Cronbach's alpha 0.86-0.95 (14). The validity and reliability of the Persian version of this questionnaire were assessed by Khorsandi et al. (2008). In their study, high internal consistency with Cronbach's alpha coefficient of 0.84 to 0.91 was reported for the CBSEI (15).

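### The stated sample-size inputs (difference 21, SD 7.2, 90% power, two-sided 0.05, 20% attrition) give 5 women per group, not 35, so at least one figure is misreported or an input is undisclosed

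*Protocol*

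**What the plan says.** The sample-size paragraph, under Data management and statistical analysis in the protocol, gives the result first: "A sample size of 70 pregnant women (35 in each group) was estimated". It names the method, "A two-sided t-test of difference between means", and then the inputs: "with the power of 90%, the type one error equal to 0.05, mean difference of 21 between groups, and standard deviation of 7.2". It adds that 20% attrition was allowed for, and attributes the calculation to the results of a 2016 study of antenatal education. Procedures sets 1:1 allocation. The Project summary and Study design repeat the total of seventy. No section gives a further input, a design factor, or sizing on a secondary outcome that would account for a larger number.

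**The concern.** The calculation is stated in full, so a reader should be able to repeat it. A difference of 21 points against an SD of 7.2 is nearly three standard deviations, and an effect of that size needs only a handful of women per group. The stated 35 cannot follow from it.

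What is at stake is the meaning of the 90% power claim. As written, the claim is attached to a difference and an SD that do not lead to the sample size. A reader of the eventual result, especially a null one, could not tell which W-DEQ difference the trial had 90% power to detect.

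**Working it through.** **Inputs, all from the protocol.** Difference 21; SD 7.2; two-sided alpha 0.05; power 90%; attrition 20%; allocation 1:1. Stated result: 35 per group, 70 in total.

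**Step 1. Standardised difference.** d = 21/7.2 = 2.92.

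**Step 2. Normal approximation.** n per group = 2(1.960 + 1.282)² / d² = 2.47, rounded up to 3. After attrition, 3/(1 − 0.20) = 3.75, so 4 per group.

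**Step 3. Exact two-sample t-test.** Power comes from the noncentral t distribution with 2n − 2 degrees of freedom and noncentrality d√(n/2).

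| n per group | Power |
|---|---|
| 3 | 76.1% |
| 4 | 92.7% |
| 5 | 98.0% |

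The requirement is 4 per group. After attrition, 4/0.80 = 5 per group, 10 in total. The stated 35 is 35/5 = 7 times that.

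**Step 4. Attempts to reproduce 35.** One-sided and two-sided tests, power of 80%, 90% and 95%, alpha divided by 2, 3 or 6, and attrition applied as n/(1 − 0.20) or n × 1.20 all give 3 to 8 per group after attrition. Exchanging the difference and the SD gives 179 per group before attrition. None of these comes near 35.

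**Step 5. Working back from 35.** 35 × 0.80 = 28 evaluable per group, so the attrition step is consistent with 28 before inflation. With 28 per group, the exact t-test reaches 90% power at d = 0.88 (0.882 before rounding). In W-DEQ points:

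- if the SD is 7.2, the detectable difference is 0.882 × 7.2 = 6.4;
- for the detectable difference to be 21, the SD must be 21/0.882 = 23.8.

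By the normal approximation, a difference of 21 with SD 24, or a difference of 6.3 with SD 7.2, gives 28 and then 35 per group. Either pair would explain the stated number; the pair of 21 and 7.2 does not.

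**Step 6. Power for the stated 21 points with 28 evaluable per group.** The SDs other than 7.2 are assumptions that show the range.

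| SD | Power for 21 points |
|---|---|
| 7.2 | essentially 100% |
| 15 | 99.9% |
| 20 | 97.1% |
| 23.8 | 90% |
| 25 | 87.0% |

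**The case against.** The best defence is that the mismatch runs in the safe direction: the trial enrols more women than its inputs require. That stands. With both stated inputs, power is essentially 100%, and the SD would have to exceed about 23.8 before power for 21 points fell below 90%. It does not rescue the calculation, because the protocol presents 35 as the result of these inputs and gives no other reason for it.

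Three stronger readings are tempting, and the documents do not support them.

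- **That the trial is underpowered.** A reader might infer this by computing power for a smaller difference, such as 10 points at a larger SD. No such difference appears in the protocol, so a low power figure obtained this way would rest on assumed values.
- **That an SD of 7.2 is impossible in this population.** Eligibility starts at 38 with no upper limit on a scale of 0 to 165, while an SD of 7.2 puts about 95% of normally distributed scores within 2 × 1.96 × 7.2 = 28 points, about the width of the moderate band alone ("a score of 38-65 represents a moderate level"). But Outcomes defines the primary outcome as a change in score, and the protocol does not say whether 7.2 is the SD of a score or of a change. The spread of baseline scores does not test the SD of a change. An open upper limit also permits a wide spread without showing one, and Procedures describes the women enrolled as having moderate and high scores. The comparison is a reason to recheck the figure, not proof that it is wrong.
- **That the detectable effect is unknown.** It is known in SD units, 0.88 with 28 evaluable per group. Only its conversion to W-DEQ points is open.

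Nor can one assume a copying error in a particular figure. The source study is not at hand, and an unstated input would explain 35 equally well.

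**Conclusion.** The sample-size statement is wrong as written and should be corrected, because the 90% power claim for the primary outcome rests on it. The error is sevenfold: 5 per group from the stated inputs against 35 stated. This conclusion needs only the protocol's own figures and the t-test it names. The documents cannot show which of the difference, the SD or the sample size is misreported, or whether an input was left out.

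The conclusion concerns a calculation that cannot be reproduced, not a shortage of women. The figures for what 70 women deliver assume exactly 20% loss in each group, and in points they depend on an SD that the protocol has yet to establish.

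**What to change.** Keep 70 women. Recheck the difference and the SD against the source study, and state for each:

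- which W-DEQ version and time point it comes from;
- whether it refers to a score or to a change in score;
- whether 7.2 is a standard deviation or a standard error.

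Then correct the wrong figure, or disclose the input that produced 35, so that the calculation can be repeated.

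Add a sentence on what the fixed sample size delivers, for example: with 35 women randomised and 28 evaluable per group, a two-sided 5% t-test has 90% power for a standardised difference of 0.88, equal to 6.4 W-DEQ points if the SD is 7.2 and 21 points if the SD is about 23.8. Label this as the detectable effect at this sample size, not as the target the trial was designed around, since nothing in the protocol shows that 0.88 was ever that target.

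The cost is protocol wording and a check of one cited source. No additional participants are needed.
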